### Aims and benefits

The study examines the outcomes of engagement with CCUs, and considers the impact of the integrated staffing model on both the outcomes and experiences of care in comparison to a clinically staffed CCU.

The quantitative component of the study explores the expectation that consumers under integrated and clinical staffing models will experience improvement in psychosocial functioning as measured by the total Health of the Nation Outcome Scale (HoNOS) [26] score following discharge from CCU care, and that no significant differences will emerge between the changes observed under each model. Equivalence testing rather than assessing for superiority or non-inferiority of the integrated staffing model is supported by:The operation of an identical model of service across both the clinical and integrated sites, hence the expectation that equivalent care will be delivered. If equivalent care was realised was a staffing model where the majority of staff are employed on the basis of their ‘lived experience’ rather than clinical expertise this would support future decision-making about staffing on the basis of secondary considerations [27] such as cost-effectiveness and consumer preference.Limitations in the quantitative evidence base relating to the impact of the integration of peer support to justify a hypothesis of superiority. Where quantitative findings are available these have tended to discuss equivalent outcomes to clinical staff. Furthermore, a failure to demonstrate superiority of the integrated model would not answer the question of whether such a staffing approach may be appropriate to be considered by other services [28].The limitations of testing a non-inferiority hypothesis with regards to establishing the equivalence of the two models where qualitative differences in the experience of care are theorised, and the impact of these on consumer outcomes is unknown.

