### Sample

The project is currently in progress. The cohort will comprise all consumers admitted to the three MSAMHS CCUs (Bayside, Coorparoo and Logan) between December 2014 and December 2017 who provide informed consent to participate. Baseline and follow-up data will be sourced from administrative datasets for the 12-month period prior to and following CCU admission and discharge respectively.

As the study takes a naturalistic observational design, the only defined inclusion criteria is acceptance for a trial of CCU based rehabilitation care. Each CCU provides a six-week assessment period to establish suitability for engagement under the model of service. Given this, consumers who are discharged prior to the conclusion of this assessment period will be excluded from the study. This exclusion criterion assists in ensuring that included participants are aligned with the model of service. This reflects a modified intention-to-treat approach [34], as participants will be included regardless of their mode of exit from the CCU (planned/unplanned (CCU initiated)/unplanned (consumer initiated).

Based on anticipated service throughput, with a median length of stay at the Coorparoo CCU of 0.9 years (inter-quartile range 0.50-1.8 years) at a point estimate in 2013, and assuming a 70 % response rate, it was expected that at least 60 consumers from the integrated staffing model and 40 from the clinical staffing model would agree to participate over the study period. This minimum sample likely reflects an under-estimate given 37 unique admissions occurred to the Coorparoo CCU in the 12-month period from July 2012. Additionally, since the opening of the Bayside and Logan CCUs 50 of the 63 consumers admitted across all three sites met the inclusion criteria (79.4 %) and 42 (84.0 %) of eligible consumers provided consent to participate.

The adequacy of the estimated minimum sample size was considered using the Epi Info™ StatCalc program [35] for unmatched or cross-sectional cohort studies. This minimum sample was estimated to provide greater than 80 % power to detect a 15 % difference in outcome on the primary outcome measure at the 95 % confidence interval using the Fleiss calculation. The acceptability of this power is supported by an emergent difference of 20 % in outcome HoNOS scores in a recent Australian study examining outcomes of a community residential service for similar consumers [36].

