### Measures

#### Primary outcome measure

The primary outcome measure will be change in psychosocial functioning as measured by total score on the HoNOS [37]. It is hypothesised that there will be no significant difference in the mean change in highest total HoNOS score recorded in the 0–12 months prior to CCU commencement and the highest score recorded 0–12 months post CCU discharge for consumers under the clinical and integrated staffing model. The total HoNOS score has been selected as the primary outcome measure as it:Has high validity, reliability and sensitivity to change, as well as routinely informing service policy and planning decisions in Australia [38];Is considered appropriate for tracking changes in social functioning over time, and more sensitive in doing so than the CANSAS (a needs based measure) [39];Has an embedded role in individual outcome assessment in Australia and New Zealand [38, 40, 41] and there is evidence that it is being regularly utilised in care planning [42, 43]Is supported by an established national assessment protocol and training processes to facilitate inter-rater reliability [38], and with evidence to support higher levels of acceptability [44] and completion than the other core measures of routine outcome suite [38]It is used and available across multiple international settings [45], increasing the replicability of the methodology.

Utilising the criterion of the highest (i.e. greatest dysfunction) score in the 12-month period pre and post CCU entry limits the risk of conflating the benefits of active rehabilitation support with the benefits associated with support and accommodation in the CCU setting.

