Planned secondary outcome measures will be derived from this assessment battery and routine administrative data sets. Secondary outcome assessment will specifically focus on mean changes in symptomatology (Brief Psychiatric Rating Scale (BPRS) [46] & Scale for the Assessment of Negative Symptoms (SANS) [47]), disability (Life Skills Profile-16 [48]), recovery orientation (Stages of Recovery Instrument (STORI-30) [49]), carer quality of life (Adult Carer Quality of Life (AC-QoL) [50]), emergency department presentations, psychiatric inpatient bed days, and psychological distress and wellbeing (MHI-38) [51]). For each of these secondary measures it is again hypothesised that no differences in mean change will emerge between the clinical and integrated staffing models.

Descriptive details of consumer characteristics and care experience will also be recorded. Relevant information will include: age at CCU commencement, gender, ethnicity, marital status, years of education, diagnosis, involuntary treatment order status, medication, length of stay, and the mode of exit from the CCU (planned/unplanned (consumer initiated)/unplanned CCU initiated).

Information about the operational costs under the integrated and clinical staffing models over the December 2014 - December 2017 period will be reported descriptively. Additional information about the operational experience under the integrated and clinical staffing models including staff retention and absences will also be reported. Estimates of the cost of ongoing service utilisation following CCU engagement based on ED Presentations and acute inpatient bed days in the 12-months post-CCU discharge will be calculated using the most recently available state-wide cost estimates.

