### Analysis

The quantitative analysis will be undertaken in SPSS Version 22 and statistical significance will be assessed at a level of 0.05:The cohort of consumers utilising the services across the three sites will be defined using descriptive statistics. Differences between the sites and staffing models will be examined using t-tests and chi-squared analyses. Assuming comparability of the cohorts is established it is planned that the data from the two integrated staffing model sites will be able to be combined.In order to answer the question of equivalence of the integrated and clinical staffing model for CCUs, differences in the total HoNOS score pre admission and post discharge will be assessed using a t-test or Mann–Whitney U test depending on the normality of the distribution.The question of whether CCU rehabilitation care results in change in specific clinically relevant outcome domains, will be answered through analysis of the secondary outcome measures. It is anticipated that data from the secondary outcome measures will be dichotomised and subjected to Mann–Whitney U analysis with appropriate correction for multiple comparisons.Predictors of change in psychosocial functioning following CCU care will be explored using hierarchical linear regression modelling. The dependent variable is the same as the primary outcome variable for the overall study, mean change in total HoNOS score pre admission and post discharge from CCU care. The independent variables will be entered cumulatively with the organisational (Level 3) variable considered first, followed by the site related (Level 2) variables and then the consumer (Level 1) variables. A hierarchical approach is appropriate given the expectation of inter-correlation between the predictors [68].

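### The aim is equivalence, but the primary analysis is an ordinary test of difference with no margin, so a non-significant result could not support the claim

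*Protocol article*

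**What the plan says.** **Aim.** The Aims and benefits section justifies "Equivalence testing rather than assessing for superiority or non-inferiority of the integrated staffing model" with three reasons. It adds that equivalent care would let staffing be decided on secondary considerations such as cost-effectiveness and consumer preference.

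**Hypotheses.** The same section expects that "no significant differences will emerge between the changes observed under each model". The Primary outcome measure section repeats this: "It is hypothesised that there will be no significant difference in the mean change in highest total HoNOS score". For the secondary outcomes, "it is again hypothesised that no differences in mean change will emerge between the clinical and integrated staffing models".

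**Analysis.** The quantitative Analysis section introduces the primary comparison with "In order to answer the question of equivalence of the integrated and clinical staffing model for CCUs" and then gives the method: "differences in the total HoNOS score pre admission and post discharge will be assessed using a t-test or Mann–Whitney U test", chosen according to normality. The general rule is that "statistical significance will be assessed at a level of 0.05".

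**Size.** The Sample section expects "at least 60 consumers from the integrated staffing model and 40 from the clinical staffing model". It reports more than 80 % power to detect a 15 % difference, by a Fleiss calculation in Epi Info.

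**Margin.** None is stated. The Design section says that principles for reporting equivalence studies were considered, and the Discussion comments on an assumption behind equivalence testing. Neither gives a margin, a confidence-interval rule or two one-sided tests.

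**The concern.** A t-test or Mann–Whitney test starts from a null hypothesis of no difference and asks whether the data contradict it. Failing to contradict it can mean that the models are alike, or that the study was too small or too noisy to tell them apart. Equivalence reverses the burden: the data must rule out differences as large as a stated margin. The article names the equivalence question but fixes the test that cannot answer it.

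The incentive also runs the wrong way. Fewer participants, more missing HoNOS ratings or noisier ratings all make a non-significant result more likely, and so make the stated hypothesis easier to confirm. Peer workers are 61 % and 56 % of full-time-equivalent staff at the two integrated sites, and the abstract expects the findings to guide similar services. An uninformative null result could be read as support for treating the two staffing models as interchangeable.

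**Working it through.** **Inputs.** From the article: 60 integrated and 40 clinical participants (Sample); significance level 0.05 (Analysis), taken as two-sided because the power statement refers to a 95 % confidence interval. The article gives no SD for HoNOS change and no margin, so effects and margins below are in SD units and are assumptions. Site clustering and confounding are ignored.

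**Step 1. The article's own figure.** Power above 80 % for a 15 % difference cannot be reproduced, because no base rate is given and the 15 % is not said to be absolute or relative. As an absolute difference in proportions (two-sided 0.05, no continuity correction, 40 v 60), power is 31 % at 42.5 % v 57.5 % and 46–52 % at 10 % v 25 %, depending on which arm has the higher rate. It passes 80 % only when one rate is close to 0 or 100 % (83 % at 0.1 % v 15.1 %, arms ordered favourably). The point made here does not depend on this. What matters is that the calculation concerns detecting a difference, so it says nothing about showing equivalence.

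**Step 2. How often the planned t-test is non-significant when the models do differ.**

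Standard error in SD units: √(1/60 + 1/40) = 0.204. Non-centrality = d / 0.204, on 98 degrees of freedom, critical value 1.984.

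| True difference d | Non-centrality | Power | Non-significant |
|---|---|---|---|
| 0.3 SD | 1.47 | 0.307 | 69 % |
| 0.5 SD | 2.45 | 0.679 | 32 % |

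**Step 3. Dependence on sample size.** At d = 0.5 SD the non-significant share is 32 % with 60 v 40, 42 % with 48 v 32 (an assumed 20 % loss) and 60 % with 30 v 20. At 0.3 SD and 48 v 32 it is 75 %. A smaller study meets the stated hypothesis more often.

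**Step 4. What 60 v 40 can deliver for equivalence.** For two one-sided 5 % tests with no true difference (normal approximation), power = 2Φ(margin / 0.204 − 1.645) − 1, set to 0 when negative.

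| Margin | margin / 0.204 − 1.645 | Power |
|---|---|---|
| 0.3 SD | −0.18 | 0 % |
| 0.4 SD | 0.31 | 25 % |
| 0.5 SD | 0.80 | 58 % |
| 0.6 SD | 1.29 | 80 % |

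At the same 1.5:1 allocation, 80 % power needs about 145 participants in total for a 0.5 SD margin and 398 for 0.3 SD.

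**The case against.** **No explicit rule.** The article never writes that p > 0.05 will be declared equivalence. It says only that differences will be assessed, and as a condensed article it may leave a margin to a fuller plan. The literal point stands. But a hypothesis of no significant difference, a 0.05 level and a difference test named as the answer to the equivalence question leave no other rule on the page. A fuller plan would have to replace the stated test, not add detail to it.

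**Error rates.** A reader might infer that the 69 % and 32 % are false-equivalence rates that should have been 5 %. The documents do not support this. Without a margin, nobody can say that 0.3 or 0.5 SD is non-equivalent, and two one-sided tests hold 5 % only for true differences at or beyond the margin. With 60 v 40 and a 0.6 SD margin, they would themselves declare equivalence about 43 % of the time at a true 0.3 SD, and rightly. The percentages are non-significance rates and nothing more.

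**Smaller samples.** The 48 v 32 figures rest on an assumed complete-case loss. The article plans multiple imputation (Procedures) and regards 60 and 40 as a likely under-estimate (Sample).

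**Rank test.** It would be too strong to say that the Mann–Whitney option removes any confidence interval for the mean difference; one can still be reported. The narrower point holds: the fallback tests a different quantity from the mean change in the hypothesis and has no stated equivalence form.

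**Caveats already given.** The Discussion concedes that allocation is not randomised, that the comparator's efficacy is not established and that generalisability is limited. A reader should therefore not infer that a staffing decision would rest on this p-value alone. These caveats temper the consequence but do not repair the test.

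**Conclusion.** The concern holds as a mismatch between aim and analysis. The article commits to equivalence, fixes a test of difference, words its hypotheses accordingly and gives no margin. A non-significant result under this plan would not support its central claim. At 60 v 40 that result would occur about 69 % of the time at a true 0.3 SD and 32 % at 0.5 SD, under the assumed SD-unit effects, equal variances and complete data. Other effect sizes change the figures but not the logic. Whether any such difference matters clinically cannot be judged until a margin is set. This needs correcting before outcomes are compared by staffing model.

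**What to change.** 1. Before any comparison by staffing model, state and justify an equivalence margin in HoNOS points. The article gives no expected change in points and no SD to anchor one, so the investigators must supply the justification.
2. Replace the primary test with two one-sided 5 % tests. Conclude equivalence only if the 90 % confidence interval for the between-model difference in mean HoNOS change lies wholly inside ± the margin; otherwise report the result as inconclusive or different.
3. Base the decision on the mean-difference interval (t-based or from a regression, bootstrap if skewed), and drop the switch to Mann–Whitney for this purpose.
4. Reword the hypotheses in Aims and benefits, Primary outcome measure, and Planned secondary outcome measures and descriptive data to match.
5. In Sample, replace the statement about detecting a 15 % difference with the equivalence power that 60 v 40 gives at the chosen margin.

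**Cost.** An amendment to wording and agreement on one margin, with no new data. An inconclusive result becomes more likely and the stated power less favourable. If the justified margin is well below 0.6 SD, the planned minimum sample is unlikely to be enough, and the report should say so.

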In addition to the primary outcome of focus, the quantitative data collection and analyses will consider the following questions:Who are the consumers who currently utilise community based residential rehabilitation services (cohort description)?Does provision of CCU rehabilitation care result in change in domains of relevance to serious and persistent mental illness between admission and discharge (secondary outcomes)?What factors predict a consumer psychosocial outcome through the provision of CCU based rehabilitation support (hierarchical linear regression modeling)?How do the operational costs associated with running a CCU under the clinical and integrated staffing models compare (description)?

The qualitative aspects of the study will facilitate detailed understanding the nature of the services under investigation. Following a pragmatic approach to grounded theory enquiry, no hypotheses are made a priori in relation to the qualitative data. Social and social-psychological phenomena underlying the consumer and staff experience of CCU based rehabilitation will be explored, including:Defining and comparing the expectations of care at the CCU under the integrated staffing model for consumers and staffComparing the experience of care in a traditional clinical staffing model with the novel integrated model for both consumers and staffExamining reflections on the experience of rehabilitation care post-discharge for consumers under both the clinical and integrated CCU staffing models.

Principles of participatory action research [29] have informed the approach to the qualitative component of the study. Both consumer and staff participants will be actively involved as co-creators of knowledge during the analysis and manuscript preparation. Additionally, this knowledge is expected to drive future service development.

The understanding of the residential rehabilitation service and the implications of the integrated staffing model achieved through this project will have implications for future service planning. The outcomes will be relevant to the staffing and processes of similar units in Australia, as well as guiding service providers internationally about novel ways of incorporating peer support into routine clinical care.

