^2^ Planned secondary outcome, examining change between Admission and Discharge for Clinical assessment battery items, and Baseline and Follow-up for Administrative data items

^*^ Planned predictor in hierarchical linear regression modelling, note that for STORI-30 change between Admission and Discharge stage will be used (reduced, stable, increased)

X Collection occasion

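### Secondary outcomes defined as mean changes are to be dichotomised and put through an unpaired Mann–Whitney test, which tests neither the stated hypothesis nor the question attached to it

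*Protocol article*

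**What the plan says.** The protocol article describes the secondary outcomes in four places.

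- **Definition** (Planned secondary outcome measures and descriptive data): "Secondary outcome assessment will specifically focus on mean changes in symptomatology", followed by disability, recovery orientation, carer quality of life, service use, and distress and wellbeing.
- **Hypothesis** (same section): for each measure, "it is again hypothesised that no differences in mean change will emerge between the clinical and integrated staffing models".
- **Question** (Aims and benefits): "Does provision of CCU rehabilitation care result in change in domains of relevance to serious and persistent mental illness between admission and discharge". The Analysis section takes it up as "The question of whether CCU rehabilitation care results in change in specific clinically relevant outcome domains".
- **Test** (Analysis): "data from the secondary outcome measures will be dichotomised and subjected to Mann–Whitney U analysis with appropriate correction for multiple comparisons".

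Footnote 2 of Table 2 (Design) sets the windows: "Planned secondary outcome, examining change between Admission and Discharge for Clinical assessment battery items, and Baseline and Follow-up for Administrative data items". No cut-point and no reason for dichotomising is given. The primary outcome, by contrast, stays on its score scale and is compared by t-test or Mann–Whitney U.

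**The concern.** Two questions are in play, and the single test named fits neither.

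1. **Do the staffing models differ in mean change?** This needs a between-model comparison of change scores. Once the data are cut in two, the comparison is of proportions above a cut-point, and the mean change is no longer being estimated.
2. **Do consumers change with care?** This is a within-person question. Mann–Whitney assumes independent groups. Used between models, it says nothing about whether anyone changed. Used on admission against discharge values, it ignores the pairing.

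The stake is a set of secondary results that do not address their own hypotheses, obtained with less power than the same data allow. The Discussion gives these analyses weight: they are to help interpret whether a change, or the lack of one, in the primary outcome is meaningful.

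**Working it through.** **Plan's own figure.** The article gives no power for the secondary outcomes, so there is nothing to reproduce. The power statement in the Sample section concerns the primary outcome only and is not used here.

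**Step 1: what Mann–Whitney does on two-valued data.** With only two values, the tie-corrected Mann–Whitney statistic equals Pearson's chi-squared multiplied by (N−1)/N. Invented example: 18/40 v 38/60.
- Chi-squared = 3.274, p = 0.0704.
- 3.274 × 99/100 = 3.241, p = 0.0718.
- Mann–Whitney without continuity correction: p = 0.0718.

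The two agree, so the planned test is a test of two proportions.

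**Step 2: cost of dichotomising, as an illustration.**

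From the document:
- 60 integrated and 40 clinical consumers (Sample, expected minimum);
- significance level 0.05 (Analysis).

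Assumed, because the document does not state them:
- normal change score with equal SD in both groups;
- true difference d = 0.5 SD;
- two-sided test;
- split at the pooled median;
- Bonferroni over eight as the correction, so alpha = 0.05/8 = 0.00625.

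*Change score kept, t-test.* Noncentrality = d × √(n1·n2/(n1+n2)) = 0.5 × √(2400/100) = 0.5 × √24 = 2.449, with 98 df.
- alpha 0.05: critical t = 1.984, power 67.9%.
- alpha 0.00625: critical t = 2.795, power 37.0%.

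*Split at the pooled median.* The cut lies approximately at 0.6 × 0.5 = 0.30 SD above the clinical mean.
- Proportion above the cut: clinical 1 − Φ(0.30) = 0.382; integrated 1 − Φ(−0.20) = 0.579; difference 0.197; pooled 0.500.
- SE under the null = √(0.25 × (1/40 + 1/60)) = 0.1021.
- SE under the alternative = √(0.382 × 0.618/40 + 0.579 × 0.421/60) = 0.0998.
- Power = Φ((0.197 − z × 0.1021)/0.0998).
- alpha 0.05 (z = 1.960): 48.9%.
- alpha 0.00625 (z = 2.734): 20.6%.

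| Analysis | alpha 0.05 | alpha 0.05/8 |
|---|---|---|
| t-test on change score | 68% | 37% |
| Median split, proportion test | 49% | 21% |

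A simulation of 8,000 trials gave 68% v 54% and 37% v 23%. The simulated split test was slightly liberal (6.3% rejections under no difference at nominal 5%), so its loss looks a little smaller, in the same direction. A split at the 80th percentile loses more: 36% and 12% by the normal approximation.

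**Step 3: number of outcomes.** The text names BPRS, SANS, LSP-16, STORI-30, AC-QoL, emergency department presentations, inpatient bed days and MHI-38, which is eight. Table 2 also marks SFS with superscript 2, which makes nine. Under Bonferroni, alpha would be 0.00625 or 0.00556. The effect on power is small, but the family has to be fixed before any correction can be applied.

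**Step 4: time windows.** Aims and benefits puts the secondary question at admission to discharge without distinction. Table 2 footnote 2 uses that window for the clinical battery only, and baseline to follow-up for administrative items.

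**The case against.** Several counter-arguments have force.

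- **The wording is provisional and the outcomes are secondary.** The article says only that this analysis is anticipated, and the primary outcome is not dichotomised. Cut-points and the correction method may properly sit in an analysis plan that is not shown. This stands and limits the severity. It does not remove the contradiction, because no choice of cut-point turns a comparison of proportions into a test of mean change, and no other test of change in these outcomes is named.
- **A reader might infer that every loss of power favours the hypothesised result.** The document does not support that. On the question of whether care produces change, Aims and benefits expects improvement, so lower power works against the expected finding. It helps only on the between-model hypothesis. Even there, the root cause is that equivalence is worded as absence of significance ("no significant differences will emerge between the changes observed under each model") with no margin stated. That would remain if the scores were kept continuous.
- **A reader might take the 79% chance of missing a 0.5 SD difference (100 − 21) as the cost of dichotomising.** It is not. With the same assumed Bonferroni correction, a t-test on the uncut score already misses it 63% of the time (100 − 37). Dichotomising adds about 16 points. Correcting for several outcomes is ordinary practice: eight independent tests at 0.05 carry a familywise error of 1 − 0.95^8 = 34%.
- **The illustration does not fit every outcome.** Presentations and bed days are counts, STORI-30 is treated as ordinal stages, and AC-QoL is completed by carers, so 60 v 40 need not be its sample. This stands.
- **The windows are already set.** Table 2 footnote 2 fixes one for each class of measure. This stands too, and only the wording of the aims needs aligning.

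**Conclusion.** The point holds as a mismatch between estimand, question and test. The outcomes are defined as mean changes, but the named analysis compares proportions, and an unpaired test cannot show whether consumers changed. This part rests on the text and needs no distributional assumption.

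The power loss is illustrative: 68% to 49% at alpha 0.05, and 37% to 21% under Bonferroni over eight. It depends on a normal change score, a median split, a 0.5 SD difference and groups of 60 and 40. The direction was the same in every case computed, while the size varies with cut-point and distribution. On the between-model hypothesis only, the loss makes the hypothesised non-significant result more likely.

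The document does not support reading this as a general bias toward the expected findings, or as a flaw in the primary test. It should be fixed, but as a defect of the secondary analysis. The eight-or-nine count and the window wording are minor inconsistencies alongside it.

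**What to change.** 1. Analyse change on each measure's own scale. For whether care is followed by change, use a paired pre-to-post analysis with a confidence interval. For staffing, give a between-model estimate of the difference in change with a confidence interval.
2. Use methods suited to the data type where a mean change on a continuous scale is not apt: counts for emergency department presentations and bed days, ordered categories for STORI-30 stage.
3. Name the multiplicity correction and the family it covers. Do not read a non-significant between-model result as equivalence unless a margin has been fixed in advance.
4. If dichotomising is kept for any measure, give the cut-point and the reason, and redefine that outcome and its hypothesis as a proportion.
5. Settle whether SFS is a secondary outcome, so that the text and Table 2 agree.
6. Reword the question in Aims and benefits to match the windows in Table 2 footnote 2.

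The cost is analysis wording only. The same data are collected at the same times from the same consumers.
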